### Data collection

All study outcomes, except the SeMaS, will be assessed at baseline, after 3 months, 6 months, and thereafter every 6 months until end of follow-up or end of the study (Table 2).

Data will be registered in case report forms (CRF). IBM Data Collection will be used as CRF. The database is developed by Nefrovisie and follows the principles of Good Clinical Practice (i.e. it has an audit trail, possibility for electronic signing, direct validation of inserted data, authorisation per form and user). Nefrovisie will also host the database for the duration of the study. The database will be archived for future research during 15 years after termination of the study.

### Statistical analysis

All statistical analyses will be performed using statistical software such as SPSS and Stata. Univariable and multivariable regression analysis will be conducted. In case of repeated measures, multilevel analysis or generalised estimating equations will be applied. Possible confounders determined a priori are age, gender, marital status, level of education, work status, cause of renal failure, prior RRT with dialysis vintage, comorbidities, albumin, body mass index, and protein energy wasting. Cumulative incidence of hospitalisation, mortality, and technique failure will be reported in Kaplan Meier curves. In case of missing data, multiple imputation techniques will be used to impute the missing values where appropriate.

Overall costs will be compared across the treatment groups and 95% confidence intervals will be estimated using bootstrapping techniques. The cost-effectiveness of different dialysis modalities will be determined using a state transition model. This model captures the changes in treatment modality, including transplantation, over time. The results of the DOMESTICO study will be used as input parameters for this model.

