### Outcomes

#### Primary outcome parameter

The primary outcome parameter is the patient’s HRQoL, a PRO, determined with the 12-item Short Form (SF-12) health survey and the Dialysis Symptom Index (DSI) [39, 40]. These questionnaires were carefully selected as Patient Reported Outcome Measures (PROMs) in nephrological care by the Dutch Kidney Patients Association, the Dutch Federation for Nephrology, Nefrovisie (the Dutch Quality Institute for Nephrology), and Leiden University Medical Center [41, 42].

The SF-12 is the shorter version of the Short Form-36 (SF-36), one of the most widely used surveys to assess HRQoL [43, 44]. The SF-36 consists of eight domains: Physical functioning, Role-physical, Bodily pain, General health, Vitality, Social function, Role-emotional and Mental health. These domains are summarised in the Physical Component Summary (PCS) score and the Mental Component Summary (MCS) score. In the SF-12 these summary scores are calculated from the 12 most important questions (explaining ~ 90% variance) of the SF-36 questionnaire [39, 45]. As the average difference in summary scores between SF-36 and SF-12 is quite small, for time-efficiency reasons, the SF-12 can be used reliably in cohort studies [46].

The DSI consists of 30 questions evaluating the severity of symptoms relevant to dialysis and ESRD patients (Table 1). Patients report the level of burden of specific symptoms on a 5-point Likert scale, options range from ‘not at all bothersome’ to ‘very bothersome’ [40].

**Table 1 Tab1:** Items Dialysis Symptom Index

1. Constipation	16. Chest pain
2. Nausea	17. Headache
3. Vomiting	18. Muscle soreness
4. Diarrhoea	19. Difficulty concentrating
5. Decreased appetite	20. Dry skin
6. Muscle cramps	21. Itching
7. Swelling in legs	22. Worrying
8. Shortness of breath	23. Feeling nervous
9. Lightheadedness or dizziness	24. Trouble falling asleep
10. Restless legs or difficulty keeping legs still	25. Trouble staying asleep
11. Numbness or tingling in feet	26. Feeling irritable
12. Feeling tired or lack of energy	27. Feeling sad
13. Cough	28. Feeling anxious
14. Dry mouth	29. Decreased interest in sex
15. Bone or joint pain	30. Difficulty becoming sexually aroused

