Direct healthcare costs, patient costs, and costs with regard to productivity losses will be assessed with a subset of questions from the Institute for Medical Technology Assessment (iMTA) Productivity Cost Questionnaire (iPCQ) and the iMTA Medical Cost Questionnaire (iMCQ) [49, 50]. To capture all health care costs for the population under research a small number of disease specific services are added to the standard iMCQ, e.g. home dialysis. Given the fact that many patients need substantial help from close relatives, also use of informal care by patients will be assessed. The costs related to the healthcare consumption, the dialysis procedures, the diagnostic tests and (over-the-counter) medication will be derived from the patient’s medical chart during the study. Unit costs will be derived from the Dutch manual for costing studies [51].

To further examine cost-effectiveness, the EuroQol-5D-5L (EQ5D-5L) questionnaire will be used. The EQ-5D-5L measures HRQoL on the following 5 domains: mobility, self-care, usual activities, pain/discomfort, and anxiety/depression. Each domain has 5 levels of functioning, ranging from ‘no problems’ to ‘extreme problems’. The EQ-5D-5L also contains a visual analogue scale on which the current health state can be indicated. The EQ-5D scores can be used to calculate utilities, which describe HRQoL on a scale from 0 (dead) to 1 (perfect health). Utilities can be combined with survival to calculate quality adjusted life years (QALYs). As outcome measure for cost-effectiveness, the costs per additional QALY will be analysed [52, 53].

All participating patients will also receive a self-management screening questionnaire (SeMaS) at baseline, in order to investigate whether self-management can predict a successful home dialysis treatment. This questionnaire shows the abilities and possible barriers for self-management by asking questions about the burden of disease, locus of control, self-efficacy, social support, coping style, anxiety, depression, and skills [54, 55].

Table 2 provides an overview of the moments when participating patients will fill in the aforementioned questionnaires.

**Table 2 Tab2:** Overview questionnaires

Visit	SF-12 and DSI	iPCQ and iMCQ	EQ-5D-5L	SeMaS
Baseline	X	X	X	X
At 3 and 6 months	X	X	X	
At 9 months and every 6 months thereafter		X		
At 12 months and every 6 months thereafter	X	X	X	

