## Discussion

Dialysis has a great impact on the HRQoL of ESRD patients and dialysis is a very expensive treatment. More than 80% of Dutch dialysis patients are treated with ICHD although home dialysis could result in a better HRQoL and could be more cost effective. Therefore, we initiated the DOMESTICO study, which will investigate the effects of home dialysis on HRQoL in relation to clinical outcomes and costs, in comparison with ICHD. This nationwide cohort study will include 1600 incident dialysis patients over a period of 3 years. At time of submission of this manuscript, 338 patients have been included.

Although a randomised controlled trial (RCT) would yield the ultimate answer to our research question, this is not in accordance with the concept of shared decision making. A patient’s choice between home dialysis and ICHD is considered too fundamental, to let it be determined by chance. Indeed, an RCT in the Netherlands comparing PD with ICHD conducted in the past, stopped early due to poor patient recruitment; only 38 patients consented to be randomly assigned to either PD or ICHD [64]. Hence, DOMESTICO is designed as a prospective, observational cohort study collecting extensive parameters to correct for confounding by indication.

The results of this study will be of great importance for future ESRD patients when choosing a treatment, as HRQoL is increasingly acknowledged by clinicians and patients as an important aspect in the decision-making process. In addition, the results with respect to clinical outcomes will ameliorate the shared decision-making process. Finally, the data could give more guidance to healthcare professionals, in particular to assess which type of patients may benefit most from home dialysis.

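### The a-priori confounder list does not name the baseline score of the HRQoL instrument being analysed, although that score is collected and modality is chosen rather than randomised

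*Protocol article*

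**What the plan says.** The Statistical analysis section gives a specific list. It opens "Possible confounders determined a priori are age, gender, marital status, level of education, work status, cause of renal failure, prior RRT with dialysis vintage" and closes with "comorbidities, albumin, body mass index, and protein energy wasting". No baseline HRQoL score is on it, and no domain of the self-management questionnaire (SeMaS).

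Both are collected. The Data collection section says "All study outcomes, except the SeMaS, will be assessed at baseline, after 3 months, 6 months, and thereafter every 6 months", and Table 2 marks SF-12, DSI and EQ-5D-5L at baseline. For SeMaS, the Secondary outcome parameters section says "All participating patients will also receive a self-management screening questionnaire (SeMaS) at baseline", with the purpose "in order to investigate whether self-management can predict a successful home dialysis treatment".

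On the model, the Statistical analysis section says only "In case of repeated measures, multilevel analysis or generalised estimating equations will be applied". It gives the baseline score no role as a covariate, as part of the outcome vector or as a reference for change.

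The Inclusion section lets patients enter from 4 weeks before to 4 weeks after dialysis starts. Those who are missed can enter at 3 months, give or take 2 weeks. The Discussion defends the non-randomised design by "collecting extensive parameters to correct for confounding by indication".

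**The concern.** Because modality follows a shared decision, home and in-centre patients may already differ in HRQoL when they start. The primary outcome is that same quantity measured later. Comorbidities, albumin and work status are partial stand-ins for the starting level. The starting level itself is measured and is not on the list.

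If the list is followed as printed, part of a 12-month difference could simply be the difference present at the outset. The Background faults earlier studies for inadequate correction for confounding, so this comparison needs to be sound on that point. The cohort is sized for EQ-5D-5L, so it is also large enough to make a modest SF-12 bias statistically significant.

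**Working it through.** **Inputs from the Sample size calculation section.** SF-12 difference 3, SD 10, α = 0.05, power 0.80, 175 per group. EQ-5D-5L difference 0.03, SD 0.20, 700 per group. About 10% loss, 800 per group.

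**The plan's own figures.** With two-sided α, n per group = 2 × [SD × (1.96 + 0.8416) / difference]².

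- SF-12: 2 × (10 × 2.8016 / 3)² = 174.4, so 175 per group. This matches.
- EQ-5D-5L: 2 × (0.20 × 2.8016 / 0.03)² = 697.7, so 698 against the stated 700. This agrees.
- Loss: 700 / 0.90 = 778, which 800 covers.

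The sample size arithmetic is sound. It uses no baseline adjustment.

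**Possible carry-over.** Let D be the baseline gap left after the listed covariates, and r the slope of follow-up on baseline score given those covariates. In a linear model with no true effect, a follow-up comparison that omits baseline is biased by r × D. Neither D nor r is in the documents, so both are assumed over a range.

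| r | D = 2: bias (share of 3 points) | D = 3: bias (share of 3 points) |
|---|---|---|
| 0.3 | 0.6 (20%) | 0.9 (30%) |
| 0.5 | 1.0 (33%) | 1.5 (50%) |
| 0.7 | 1.4 (47%) | 2.1 (70%) |

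If D is zero, there is no bias.

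**Chance of a false finding.** After 10% loss, 800 × 0.90 = 720 per group remain. The standard error of the difference is 10 × √(2/720) = 0.527. With no true effect, the chance of a significant result is 1 − Φ(1.96 − rD/0.527) + Φ(−1.96 − rD/0.527).

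- D = 2: 21% at r = 0.3, 76% at r = 0.7.
- D = 3: 40% at r = 0.3, 98% at r = 0.7.

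These use the full SD of 10 and are illustrations, not forecasts.

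**Does adjustment cost power?** If r is read as a correlation and the comparison is with an analysis using no covariates, the SF-12 requirement becomes 174.4 × (1 − r²). That is 159, 131 or 89 per group for r = 0.3, 0.5 or 0.7, instead of 175. The gain over an analysis that already uses the listed covariates is probably smaller, but there is no loss.

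**Does the repeated-measures model solve it?** Not by its name alone. If baseline is one of the repeated outcomes and modality enters as a main effect, the starting gap is part of the estimate. Conditioning on baseline, or a modality-by-time contrast, would deal with it. The article specifies neither.

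**The case against.** The strongest reply is that the list is one of possible confounders and is not declared exhaustive. A multilevel or GEE model can take baseline in as a covariate or as a repeated outcome, and an article may leave that to the full protocol or analysis plan, which is not shown. This stands in part: the documents do not show that the primary analysis will be unadjusted for baseline. But the list is detailed enough to name albumin and protein energy wasting, and it omits the earlier value of the primary outcome. That is a gap in what is printed, not only a detail deferred.

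A reader might infer that baseline HRQoL is the strongest available confounder and that home dialysis will look falsely better. No figure supports the first. On the second, the Background says the home population has become older and often has several comorbidities, so even the direction of bias is unknown.

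The size is assumed, and the listed covariates may absorb much of any gap. That objection stands in full.

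Adjustment can also harm. For patients included at about 3 months, the first score follows treatment, and conditioning on it could remove real effect. This stands, and it shapes the fix.

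Two further readings are tempting. One is that adjusting for albumin, body mass index and protein energy wasting is wrong because nutritional status is also a recorded outcome. Adjusting for a baseline value of something followed later is ordinary practice, and the article does not say these covariates are updated over time. The other is that SeMaS must be on the list. Its stated purpose is prediction, and its case as a confounder is plausible but weaker.

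**Conclusion.** The point holds in limited form. The printed list leaves out the baseline score of the analysed instrument in a study where modality is chosen, the score is collected, and the target is a later between-group difference in the same score. A residual starting gap could therefore pass into the primary result. With an assumed residual gap of 2 to 3 points and a slope of 0.3 to 0.7, that is about 0.6 to 2.1 points, or 20% to 70% of the 3-point target, in either direction. The documents fix neither assumption, and a gap fully absorbed by the listed covariates would leave no bias.

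**What to change.** - Add the baseline score of the instrument being analysed (SF-12 physical or mental summary, DSI, EQ-5D-5L) to the adjustment set. In the primary model, estimate the modality effect on follow-up scores conditional on it, for patients included within 4 weeks either side of starting dialysis.
- Do not treat the first score of patients included at about 3 months as a pre-treatment baseline. Analyse them separately, or leave them out of the baseline-adjusted primary model.
- Add a sensitivity analysis restricted to questionnaires completed before the first dialysis session.
- SeMaS domains may be added as a further sensitivity adjustment.
- Settle this before outcome data are analysed.

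**Cost.** No new data collection is needed. Baselines taken shortly after the start may already carry some modality effect, so the adjusted estimate may be somewhat attenuated. Late entrants contribute less to the primary model, and the article does not say how many there will be. For SF-12 the margin is wide: 720 expected per group against 175 needed. For EQ-5D-5L it is narrow before any gain from adjustment (720 − 698 = 22 per group), which favours a separate analysis of late entrants over dropping them there.

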### Study population

All patients, aged 18 years and older, with ESRD that start with a form of dialysis in the participating centres, between December 2017 and December 2020, are eligible for this study. These patients are allowed to have a history of renal replacement therapy (RRT), however they have to (re) start dialysis during the study period for example due to kidney transplant failure (with or without previous dialysis). All these patients are defined as ‘incident patients’. Prevalent dialysis patients, and patients with a life expectancy shorter than 3 months or an expected kidney transplantation within 3 months, are excluded. Patients have to provide written informed consent before participating in the study.

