### Inclusion

Patients are included in the period within four weeks before to four weeks after start of dialysis. If patients are missed for inclusion within this timeframe (for example, due to acute start of dialysis), they can be included at 3 months (± 2 weeks) after start of dialysis. Start of dialysis is defined as the first PD session performed at (a nursing) home (excluding PD-training) or, in case of ICHD, the first haemodialysis session performed in a centre (excluding continuous RRT).

The first patient was included in December 2017 and the study has currently started in 45 centres with 338 participating patients (Fig. 2).

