### (Early) termination

For each participating patient, the study ends on 20 December 2021. Early study termination occurs if the patient withdraws from the study or stops dialysis treatment. Reasons to stop dialysis include kidney transplantation, recovery of kidney function, the wish to stop dialysis, or death.

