#### Secondary outcome parameters

Secondary outcome parameters are hospitalisation, mortality, other clinical parameters, costs, and technique failure.

The cause of each hospitalisation episode will be categorised into the following categories (using ICD-10 codes) [47]:
Cardiac (including myocardial ischaemia/infarction, cardiac arrest/arrhythmia, cardiac failure, fluid overload/pulmonary edema, haemorrhagic pericarditis);Vascular disease (including pulmonary embolus, stroke, cerebrovascular haemorrhage, ruptured vascular aneurysm, mesenteric infarction, peripheral arterial disease);Infection, non-dialysis related (including bacteraemia/sepsis, cardiac infection, HIV, osteomyelitis, respiratory infection, urinary tract infection);Dialysis related (including dialysis access infection, peritonitis, PD catheter leakage/exchange/removal, fistula operation, renal fluid overload, bleeding);Malignancy;Bleeding, non-dialysis related (including intracranial bleeding, gastro-intestinal bleeding, other causes of bleeding);Other causes.

Mortality will be categorised into the following categories (using ERA-EDTA codes) [48]:
Sudden death ‘with unknown cause’;Cardiac (including myocardial ischaemia/infarction, cardiac arrest/arrhythmia, cardiac failure, fluid overload/pulmonary edema, haemorrhagic pericarditis);Vascular (including pulmonary embolus, stroke, cerebrovascular haemorrhage, ruptured vascular aneurysm, mesenteric infarction, peripheral arterial disease);Infectious, dialysis related (including dialysis access infection, peritonitis);Infectious, non-dialysis related (including bacteraemia/sepsis, cardiac infection, HIV, osteomyelitis, respiratory infection, urinary tract infection);Malignancy;Bleeding (including dialysis related bleeding, intracranial bleeding, gastro-intestinal bleeding, other causes of bleeding);Overall deterioration in clinical condition/stopping dialysis;Other causes.

Besides hospitalisation and mortality, several clinical parameters will be recorded including blood pressure and use of antihypertensive drugs, haemoglobin and use of erythropoiesis-stimulating agents, phosphate levels and use of phosphate binders, vascular access parameters, and nutritional status.

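### The a priori confounder list leaves out residual kidney function at the start of dialysis, so any imbalance not captured by the listed covariates could bias the modality comparison

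*Protocol article*

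**What the plan says.** The Statistical analysis section sets out the adjustment set: "Possible confounders determined a priori are age, gender, marital status, level of education, work status, cause of renal failure", followed by "prior RRT with dialysis vintage, comorbidities, albumin, body mass index, and protein energy wasting". Nothing in the wording marks these as examples. Residual kidney function, in any form (GFR, clearance or urine output), is not among them.

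It is not named elsewhere as a covariate either. Under Secondary outcome parameters, "several clinical parameters will be recorded including blood pressure and use of antihypertensive drugs, haemoglobin and use of erythropoiesis-stimulating agents, phosphate levels", and the sentence ends with phosphate binders, vascular access and nutritional status. The nearest wording is in (Early) termination: "Reasons to stop dialysis include kidney transplantation, recovery of kidney function, the wish to stop dialysis, or death". That concerns leaving the study, not the patient's state at entry.

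Three other statements bear on the point:

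- The Discussion explains why measured covariates carry the comparison: "DOMESTICO is designed as a prospective, observational cohort study collecting extensive parameters to correct for confounding by indication".
- The Study population section admits restarts: "These patients are allowed to have a history of renal replacement therapy (RRT), however they have to (re) start dialysis during the study period".
- The Inclusion section says of patients missed around the start, for example because of an acute start, that "they can be included at 3 months (± 2 weeks) after start of dialysis".

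**The concern.** Without randomisation, the modality effect is only as good as the adjustment set. Every patient in this cohort is at the start, or restart, of dialysis. How much kidney function remains at that moment can plausibly differ between a planned start, an acute start and a restart after transplant failure. These routes need not be spread evenly over the modalities: the Inclusion section dates a PD start from the first session at home, after training, and an ICHD start from the first session in a centre.

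Remaining function is also plausibly related to the outcomes: fluid-related and other DSI symptoms, blood pressure, haemoglobin, phosphate and survival. A variable linked to both modality and outcome, and missing from the model, can make one modality look better or worse than it is. What is at stake is the study's main claim, because the Background faults most earlier studies for inadequate correction for confounding.

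**Working it through.** **1. The plan's own figures.** Inputs from Sample size calculation: SF-12 difference 3, SD 10; EQ-5D-5L difference 0.03, SD 0.20; α = 0.05 (two-sided reproduces the figures); power 0.80. The formula is n per group = 2 × (1.960 + 0.842)² × (SD/difference)².

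- SF-12: 2 × 7.849 × (10/3)² = 174.4, so 175 (stated 175).
- EQ-5D-5L: 2 × 7.849 × (0.20/0.03)² = 697.7, so 698 (stated 700).
- Loss to follow-up: 700/0.90 = 778, rounded up in the plan to 800. With 10% loss, 800 × 0.90 = 720 per group remain.

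The sample sizes hold, and adding a covariate changes none of them.

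**2. What the listed covariates capture.** Cause of renal failure and prior RRT with vintage describe the route to dialysis. Albumin, body mass index and protein energy wasting describe nutrition. Each may correlate with remaining function, but none measures it. Planned versus acute start is not listed either.

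**3. Size of a possible bias (illustration).** The documents give neither input, so both are assumptions:

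- d = difference between groups in residual function, in SD, that remains after the listed covariates;
- r = partial correlation of residual function with the outcome, read as a standardised slope.

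Bias ≈ d × r × SD of the outcome.

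| d | r | SF-12 (SD 10) | share of 3 | EQ-5D-5L (SD 0.20) | share of 0.03 |
|---|---|---|---|---|---|
| 0.3 | 0.1 | 0.3 | 10% | 0.006 | 20% |
| 0.3 | 0.2 | 0.6 | 20% | 0.012 | 40% |

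**4. What this does to the test.** For a simple two-group comparison of SF-12 scores at 720 per group, SE = 10 × √(2/720) = 0.527. With no true difference and a bias b, the two-sided 5% test rejects with probability 1 − Φ(1.96 − b/SE) + Φ(−1.96 − b/SE). For b = 0.3 this is 8.8%, and for b = 0.6 it is 20.7%. The EQ-5D-5L gives the same rates, because the bias is the same in SD units.

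**5. Range.** With d from 0.1 to 0.5 and a slope of 0.5 to 3 SF-12 points per SD of residual function, the bias runs from 0.1 × 0.5 = 0.05 to 0.5 × 3 = 1.5 points. That is 2% to 50% of 3 points, with rejection rates from 5.1% to 81%. The width of the range shows that the documents do not settle the size. No figure is offered for mortality, since the article states no target effect for it.

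**The case against.** The strongest reply has four parts.

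**The list may not be complete.** The article calls these possible confounders, introduces the clinical parameters as a partial list, and condenses a protocol and CRF that are not shown. Residual function may well be recorded. That stands as a caution: a reader should not infer that the study fails to collect it. But recording a variable does not put it into the adjustment set, and the article states that set itself.

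**The confounding is not documented.** Nothing in the article shows that remaining function differs by modality or affects SF-12, DSI or EQ-5D-5L scores. Recovery of function as a reason for exit says nothing about baseline imbalance. This stands. A reader might infer that the omission favours one modality in a known direction; the documents do not support that.

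**Other information absorbs part of it.** The listed proxies take up some of any imbalance. The Data collection section and Table 2 also place the outcomes at baseline, with repeated-measures models to follow. So a reader who concludes that a raw difference would pass wholly unadjusted goes too far, and the d that matters is what remains after adjustment. The relief is partial. The article does not say that baseline outcomes will be adjusted for, the first measurement can fall after the start (up to four weeks, or about 3 months for late inclusions), and baseline HRQoL would not repair the mortality comparison.

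**Large error rates come from chosen inputs.** With d = 0.5 and r = 0.2, the EQ-5D-5L bias is 0.5 × 0.2 × 0.20 = 0.020, and a test at 700 per group would reject about 46% of the time. That figure pairs high assumed inputs with a component of a secondary outcome, and should not be read as the expected error rate.

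**Conclusion.** The point holds as a gap in a stated adjustment set. Residual kidney function at the start is absent from the a priori list, the listed covariates stand in for it only partly, and the design depends on that list. Any imbalance left after the listed covariates could bias the modality effect on HRQoL, mortality and the clinical parameters.

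The size is unknown. The range of 0.3 to 0.6 SF-12 points rests wholly on the assumed inputs of 0.3 SD and 0.1 to 0.2. It is below the 3-point difference but not negligible next to a standard error of about 0.53. The change is worth making because it is cheap and the comparison has no other protection; confidence that the bias matters in practice is moderate.

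**What to change.** Add residual kidney function to the a priori list in Statistical analysis. Define it as the last routinely available eGFR, with urine output where charted, before the first dialysis treatment of the current dialysis episode.

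- **Time point.** Count any PD training as treatment, since the article's own PD start excludes training. For restarts, use the current episode. For patients included at 3 months, take the pre-start value from the chart.
- **Use.** Enter it as a baseline covariate in the HRQoL, mortality and clinical-parameter models. Do not adjust for values measured after the start, which the modality may itself have changed.
- **Missing values.** Use the planned multiple imputation, with planned versus acute start in the imputation model where recorded. Missingness may depend on the route to dialysis and on the unseen value, so report results with and without the covariate as a sensitivity analysis.

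**Cost.** One chart value, one more covariate and a wording change, with no extra test. At submission 338 of 1600 patients had been included, so about 79% (1262/1600) were still to come, and retrospective retrieval is needed mainly for those already enrolled and for late inclusions. The downside is an imperfect measure, with gaps concentrated in acute starters and restarts. If the full protocol or CRF already holds the value, only the analysis text changes.

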*SF-12* Short Form-12, *DSI* Dialysis Symptom Index, *iPCQ* Institute for Medical Technology Assessment (iMTA) Productivity Cost Questionnaire, *iMCQ* iMTA Medical Cost Questionnaire, *SeMaS* self-management screening questionnaire

Finally, technique failure rate of home dialysis, defined by a composite outcome of death or transfer to ICHD, will be assessed. Both a 30-days and a 180-days definition of technique failure will be used according to the minimum number of days the patient received ICHD after cessation of home dialysis [56]. Permanent technique failure is defined by death or transfer to ICHD (using the 180-days definition), or cessation of dialysis. Death-censored technique failure will be reported separately. Transfer to kidney transplantation is not considered to be technique failure and will also be reported separately [56].

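### Cumulative incidence of hospitalisation, mortality and technique failure is to be shown by Kaplan-Meier, although transplantation, recovery and, for some outcomes, death are competing events; if these are censored, the curves overstate actual risk

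*Protocol article*

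**What the plan says.** The Statistical analysis section of the protocol article fixes both a quantity and an estimator: "Cumulative incidence of hospitalisation, mortality, and technique failure will be reported in Kaplan Meier curves". It names no competing-risk method for these outcomes.

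The section on (early) termination sets when observation ends: "Early study termination occurs if the patient withdraws from the study or stops dialysis treatment". It adds: "Reasons to stop dialysis include kidney transplantation, recovery of kidney function, the wish to stop dialysis, or death". Study population removes only imminent cases: "patients with a life expectancy shorter than 3 months or an expected kidney transplantation within 3 months, are excluded". Later transplantations therefore fall within follow-up, which can last up to 48 months.

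The section on secondary outcomes defines the main version as "technique failure rate of home dialysis, defined by a composite outcome of death or transfer to ICHD, will be assessed". A second version reads: "Permanent technique failure is defined by death or transfer to ICHD (using the 180-days definition), or cessation of dialysis". Two further statements bear on censoring: "Death-censored technique failure will be reported separately", and "Transfer to kidney transplantation is not considered to be technique failure and will also be reported separately". The latter does not say whether a transplanted patient is censored in the technique-failure curve or counted as having had a competing event.

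**The concern.** Kaplan-Meier estimates a cumulative incidence only if every censored patient could still have the event later. A patient who has died cannot be hospitalised. A transplanted patient cannot die on dialysis or move to ICHD while remaining in the cohort. If such patients are censored, one minus Kaplan-Meier describes a hypothetical setting in which nobody is transplanted, recovers or (for some outcomes) dies first. It is never below the proportion who actually have the event.

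The article hypothesises at least comparable clinical outcomes with home dialysis, and its Discussion says the clinical results will support shared decision-making. A patient choosing a modality would read the curves as absolute risks. Because the article names the method, this is not a detail left open: an analysis plan that followed the sentence would carry the problem forward.

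**Working it through.** **Which event competes with which outcome, from the article's definitions**

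- All-cause mortality: transplantation and recovery compete. Death is the event.
- Cause-specific mortality: the same, plus death from other causes.
- Hospitalisation: transplantation, recovery and death.
- Technique failure (death or transfer to ICHD): transplantation and recovery. Death is a component.
- Death-censored technique failure: transplantation, recovery and death.
- Permanent technique failure: transplantation. Cessation of dialysis is an event, so recovery may count as an event; the text leaves this open.

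**Inputs**

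The article gives no event rate or cumulative incidence for these outcomes, so there is no stated figure to reproduce.

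- Death: 45% five-year survival (Background). With a constant hazard, −ln(0.45)/5 = 0.160 per year.
- Assumed, not in the article: transplantation 0.05 to 0.15 per year, transfer to ICHD 0.20 per year, first hospitalisation 0.60 per year. Recovery is left out; adding it would enlarge the excess wherever it competes.

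**Formulas** (event hazard L, total competing hazard c, time t)

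- One minus Kaplan-Meier: 1 − exp(−L·t)
- Actual cumulative incidence: L/(L+c) × [1 − exp(−(L+c)·t)]

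The second formula was checked by simulation at 4 years with L = 0.160 and c = 0.15: 0.367 simulated against 0.366.

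**Example.** Mortality at 3 years with c = 0.15:

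- One minus Kaplan-Meier: 1 − exp(−0.479) = 38.1%.
- Actual: 0.160/0.310 × [1 − exp(−0.929)] = 0.516 × 0.605 = 31.2%.
- Excess: 6.9 points.

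**Results over transplantation hazards of 0.05 to 0.15 per year**

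| Outcome | L | c | Year | 1−KM (%) | Actual (%) | Excess (points) |
|---|---|---|---|---|---|---|
| Mortality | 0.16 | 0.05–0.15 | 1 | 14.8 | 13.7–14.4 | 0.4–1.0 |
| | | | 3 | 38.1 | 31.2–35.6 | 2.5–6.9 |
| Composite technique failure | 0.36 | 0.05–0.15 | 1 | 30.2 | 28.2–29.5 | 0.7–2.0 |
| | | | 3 | 66.0 | 55.3–62.1 | 3.9–10.7 |
| Death-censored technique failure | 0.20 | 0.21–0.31 | 1 | 18.1 | 15.7–16.4 | 1.7–2.5 |
| | | | 3 | 45.1 | 30.7–34.5 | 10.6–14.4 |
| First hospitalisation | 0.60 | 0.21–0.31 | 1 | 45.1 | 39.4–41.1 | 4.0–5.7 |
| | | | 3 | 83.5 | 61.7–67.6 | 15.9–21.8 |

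**Between groups.** Give both groups the same death hazard of 0.160, with c = 0.05 in one and 0.15 in the other. The Kaplan-Meier curves coincide, but the actual risks differ: 26.1% against 23.8% at 2 years (2.3 points) and 43.2% against 36.6% at 4 years (6.6 points). With equal event and competing hazards, the distortion is the same in both groups.

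**The case against.** The best defence has four parts.

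1. **Death is partly handled.** It is a component of technique failure as defined, and the death-censored version is a supplementary report in which censoring death is the stated definition. This stands. A reader might infer that death, transplantation and recovery compete with every outcome, but death cannot compete with all-cause mortality or with the composite. Transplantation still competes with both.

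2. **No difference between groups is shown.** This also stands. A reader might infer that the comparison of home dialysis with ICHD is biased. The article gives no transplantation, recovery, hospitalisation or death rates by group, and technique failure concerns home dialysis only, so that curve has no ICHD counterpart. What remains is a possibility.

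3. **The larger figures are late and mostly assumed.** Recruitment runs from December 2017 to December 2020 and the study ends on 20 December 2021, so only patients enrolled in about the first year can reach 3 years. The sample size refers to about 12 months of follow-up, where the excess is small except for hospitalisation. Every hazard but death is an assumption. The use of first hospitalisation is another, since the article records each episode.

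4. **The article does not say that transplanted patients are censored.** True; it says only that transplantation is reported separately. But Kaplan-Meier is the only estimator named, and it has no other place for such patients.

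One further limit concerns patients who stop dialysis by choice. Censoring them before death could bias the mortality curve downwards, so not every curve need err upwards. The mortality categories include one that covers stopping dialysis, so at least some of these deaths are meant to count.

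**Conclusion.** The point holds in a limited form. The article pairs cumulative incidence with an estimator that does not deliver it when its own termination events are censored. For transplantation, recovery and (where it competes) death, the direction is certain: the curve lies at or above the actual risk. The size depends on hazards that the article does not give. Under the assumptions above, the excess at 1 year is about 2 points or less for mortality and composite technique failure and 4 to 6 for first hospitalisation. By 3 years it is several points to about 20, depending on the outcome. All figures assume constant hazards and treat the quoted five-year survival as a death rate on dialysis.

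The documents do not support a claim that the modality comparison is biased by a known amount, or that the study's main conclusion is at risk. These are secondary outcomes, and the primary quality-of-life analysis and the sample size do not depend on this sentence. It should be corrected before the curves are produced.

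**What to change.** Replace the Kaplan-Meier sentence in Statistical analysis with wording such as:

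> Cumulative incidence will be estimated with the Aalen-Johansen estimator, with transplantation and recovery of kidney function as competing events, and death as well for hospitalisation, cause-specific mortality and death-censored technique failure; for permanent technique failure, cessation of dialysis remains an event as defined.

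Keep Kaplan-Meier only where no competing event remains. State also whether recovery counts as cessation of dialysis in permanent technique failure, and how a death after a patient chooses to stop dialysis enters the mortality curve.

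The cost is a sentence or two of analysis wording. The estimator is available in standard software, including Stata, which the article already names. The article distinguishes the reasons for ending dialysis, so no new data collection appears to be needed.
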